# 9. Fortified Thiakry

- 1. **Premix Composition used by LDB for the Thiakry**

The premix for Thiakry fortification is developed by Danone R&D laboratory in France, for Danone Communities, which is a stockholder of LDB. The table of composition has been emitted from this document, due to privacy of information. It is shared in % of Recommended Dietary Allowance (RDA) for different targets (children from 1 to 3 years old, children over 3 years, and pregnant women) in Annex 1.

- 1. **Mechanism of action**

Use of iron EDTA (NaFeEDTA) for food fortification is becoming increasingly common, due to its higher absorption potential compared with sulfate iron, which was previously more common. Its absorption is 2 to 3 times greater than iron sulfate or iron fumarate (FAO/WHO, 2006) and it also increases the rate of absorption of naturally occurring iron (Van Stuijvenberg, 2008). EDTA iron is absorbed by normal physiological mechanisms. When NaFeEDTA is present in a meal, half of the iron is exchanged with naturally occurring iron and EDTA partially protects iron from inhibitory effects. Cereal inhibitors of iron absorption are phytates (i.e. sorgho) and polyphenols (i.e. millet) (Lestiennes, 2004). EDTA iron is particularly effective when added to cereals rich in absorption inhibitors (Troesch, 2010; De-Regil, 2011).

Iron bioavailability depends on dietary characteristics of population (WHO/FAO, 2006). According to guidelines on food fortification with micronutrients (Allen, 2006), there are 3 levels of bioavailability used to characterize typical diets.

- Low 1–9%: Simple, low-diversity diet based on cereals, roots or tubers, with negligible amounts of meat, fish, poultry or ascorbic acid-rich foods. Diet high in foods that inhibit iron absorption such as maize, beans, whole wheat flour, and sorghum.

- Intermediate 10–15%: Diet of cereals, roots or tubers, with some foods of animal origin (meat, fish or poultry) and/or containing some ascorbic acid (from fruits and vegetables)

- High >15%: Diversified diet containing greater amounts of meat, fish, poultry and/or foods high in ascorbic acid.

According to a 2012 study performed on micronutrient deficiencies in Senegal, daily meat consumption is rare in children at a national level (MI/COSFAM, 2012). 40.2% eat beef one to 3 times a week and 43.6% once a month. Globally, Senegalese children are not high consumers of leafy vegetables. Main leaves consumed are hibiscus, moringa, and baobab: 46.4 % consume hibiscus leaves at least one to 3 times a week and 45.6% rarely or never; 36.2% consume moringa leaves at least one to 3 times a week and more than the half (52.1%) rarely or never; and 34.5% consume baobab leaves at least one to 3 times a week and 53.9 rarely or never. Oranges (44.7%) and lemons (33.1%) are regularly consumed by children (at least once a week). On average, more than half of children occasionally or rarely eat fruits rich in vitamin C.

In the north of Senegal, the typical diet is rich in cereals (millet, rice) but poor in fish, poultry, and vitamin C-rich fruits. Meat consumption may be higher than the rest of Senegal but likely insufficient to reach a level of bioavailability higher than 10%. The level of green leafy vegetables, oranges, and lemons is likely inferior to the rest of the country. We therefore estimate that the level of iron bioavailability is between 5 and 10%.

With these low levels of iron bioavailability in typical diets (estimated between 5 and 10%), the dose of iron recommended by FAO and WHO is between 5.8 mg/day and 11.6 mg/day for children 1-3 years old and between 6.3 mg/day and 12.6 mg/day for children 4-6 years-old (WHO/FAO, 2006). However, using EDTA iron, absorption rates are increased by 2 or 3 times. Doses to cover daily needs must be divided according to the same rates.

Iron fortification levels used in another study performed in Bengladesh in infants 6-24 months was 3.3 mg of fumarate iron, which allowed the observation of a significant decrease of proportions of anemic children (Talukder, 2009). A study performed in Kenya in school children showed significant results with lower doses of EDTA iron (2.5 mg) in micronutrients powder (MNP) spread on a maize porridge for household-level fortification (Macharia-Mutie, 2012). In Kenya, another study showed that MNP containing 2.5 mg of iron EDTA and rich in vitamin C and phytases gave the same results (Troesh, 2011).

- 1. **Toxicity-Safety**

EDTA is a food additive. Its use has been approved by the FAO/WHO Expert Committee on Food Additives at the dose of 0.2 mg of iron per kg of bodyweight and per day (FAO/WHO, 2007). In to a recent study, a dose of 2 mg of NaFeEDTA was administered every day to children between the ages of 6 to 8 months, without exceeding recommended daily doses. EDTA iron is not toxic, according to different simulated scenarios corresponding to variable prevalence of underweight in children (thus likely able to surpass accepted limits per kg of weight) (Yang, 2011). In a study performed in China, a millet porridge was fortified with 2 mg of iron FeSO₄ or NaFeEDTA (first study) and with 4 mg of FeSO₄ iron or a mix of 2 mg of FeSO₄ and NaFeEDTA (second study) and given to children aged 24 to 31 months to test absorption of different combinations in a complementary product rich in phytates, with no adverse effects being reported (Chang, 2012).

# 10. Test Procedures

**10.1.** **Information and study recruitment**

A meeting will be held along each milk collection route, gathering all heads of households, in order to explain:
- Causes and consequences of anemia and the fact that LDB will make available to herders fortified Thiakry that fights against anemia
- The terms of the study, which are:

- the objectives in terms of milk collection
- the lottery defining the two intervention groups: the households receiving free fortified Thiakry for all children aged 2 to 5 years in the household and the households receiving no incentive but having the opportunity to buy fortified Thiakry directly from LDB if they wish
- the number of data collection rounds by enumerators for households etc.

- That mothers and children will have a drop of blood collected (finger prick) to measure their hemoglobin levels. The results will be immediately available and provided to families. In cases of severe anemia in children, IFPRI will facilitate transportation and will cover the price of the consultation and the cost of treatment at the nearest health center.

Household heads will leave the information meeting with an explanatory note of the study (in French and Fulani) and a form of intent to participate in the study (in French and Fulani). The form must be returned, signed by the head of household and their spouse, at the second meeting 10 days later, which will be establish the milk collection targets (contracts with LDB).

When the enumerators go to the households to begin data collection, they will read a document covering all the important aspects of the study and will obtain signature on a two-part informed consent form, targeting the household heads and the mothers.

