**Methodology**

**1. Overall objective, specific objectives, type of study, and number of subjects**

*Overall objective:* to demonstrate the "Value Chain" concept in a contractual agreement linking the Laiterie du Berger and milk producers in the area of Richard Toll, Senegal.

*Specific objectives:* to compare the results of a fortified Thiakry intervention versus a control group, concerning:
- Increasing the volume of milk and the frequency of collection during the dry season
- Reducing the prevalence of anemia among children aged 2 to 5 years

*Type of study:* cluster randomized control trial, comparing households receiving fortified (with iron) Thiakry to control households receiving no intervention. Children 2 to 5 years at baseline will be visited 6 months and 1 year from the beginning of the study.

*Number of required subjects:* 700 families of herders in total.

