# 8. Conditions of the lottery

The two groups will be chosen by lottery at the first information-sharing meeting. The draw will define the households receiving free fortified Thiakry for all children aged 2 to 5 years within their household (treatment group) and the households not receiving fortified Thiakry during the study (control group), who will receive in kind compensation at the end of the study as thanks for their participation.

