**10.4.** **Intervention**

The distribution phase of the incentive will last 6 months, from January 2013 to July 2013. The incentive of fortified Thiakry will be distributed daily by the milk collectors. Participants in the study who are part of the treatment group will have the daily opportunity to buy fortified Thiakry directly from the milk collection truck. During the study, if a herder responsible for the milk container has committed to providing a certain quantity of milk daily to LDB and does not honor their commitment one or two days in the same week, they will receive a warning (if they are in the treatment group). If the herder does not provide milk for 3 or more days in the week and is in the treatment group, they will not receive the fortified Thiakry the following week.

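### The protocol gives no single rule on who may buy fortified Thiakry: controls are offered it for sale although described as untreated, the treatment arm is described as both given it and buying it, and the sample size makes no allowance for control purchase

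*Protocol*

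**What the plan says.** **Control arm.** Three places describe it.
- Summary, Methodology item 1: "control households receiving no intervention".
- Section 8: "the households not receiving fortified Thiakry during the study (control group".
- Section 10.1, in the terms explained at the route meetings: "the households receiving no incentive but having the opportunity to buy fortified Thiakry directly from LDB if they wish".

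**Treatment arm.** Section 10.1 promises "the households receiving free fortified Thiakry for all children aged 2 to 5 years in the household", and section 8 says the same. Section 10.4 first says that the milk collectors hand out the incentive every day. Its next sentence says that participants who are "part of the treatment group will have the daily opportunity to buy fortified Thiakry directly from the milk collection truck". It then withholds the product for the following week from treatment herders who miss three or more days in a week. It does not say whether they may buy during that week.

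**Sample size.** Section 7 assumes anemia prevalence of 75% against 60%, with 165 children per group, 80% power and a one-sided 5% test. It adds a further 20% for households that may not be analysable. The reasons given are non-participation, missed milk targets and incomplete consumption in the treated group. Purchase by controls is not among them.

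**The concern.** Access to the product defines the contrast between the arms, and the sections differ on it. Section 10.1 gives the buying option to controls, while section 10.4 gives it to the treatment group. Staff running meetings and trucks on four collection routes could apply different rules and each find support in the text.

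For anemia, a control household that buys the product is partly treated, which pulls the comparison toward no difference. Some purchase is plausible. The offer is made at the meeting that explains anemia and presents the product as a remedy, and section 10.2 plans an anemia awareness campaign in the area. If purchases are not recorded, a null anemia result could not be told apart from a contaminated control arm.

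For the milk contract outcome, the unclear point is what the incentive consists of: a free bonus, a right to buy, or both.

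**Working it through.** **1. The sections side by side**

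| Place | Control | Treatment |
|---|---|---|
| Summary, Methodology 1 | no intervention | receives product |
| Section 8 | does not receive product during the study | free product for children 2 to 5 |
| Section 10.1 | no incentive, may buy | free product for children 2 to 5 |
| Section 10.4 | not mentioned | daily distribution, and may buy |

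No section states a purchase rule for both arms.

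**2. Reproducing the plan's figure**

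Inputs from section 7: p1 = 0.75, p2 = 0.60, d = 0.15, power 80%, alpha 5%. With p̄ = (p1 + p2)/2 = 0.675:

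n = [z_α √(2p̄(1−p̄)) + z_β √(p1(1−p1) + p2(1−p2))]² / d²

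Continuity correction: n_c = (n/4)·[1 + √(1 + 4/(n·d))]²

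- Two-sided: n = 151.9, n_c = 164.9, so 165 per group and 330 in total, as stated.
- One-sided, as section 7 words it: n = 119.5 (120), n_c = 132.5 (133).

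The stated 165 is therefore the two-sided, corrected figure. Sections 7 and 11.2 both specify one-sided tests, so power is shown both ways. A design effect of 1 + (2 − 1) × 0.3 = 1.3 gives 330 × 1.3 = 429, stated as 430. The 165 per group is thus the size before clustering and attrition.

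**3. Effect of control purchase**

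Let c be the share of control children who eat bought product and gain the full effect. The documents give no value, so c is an assumption. Control prevalence becomes 0.75 − 0.15c and the treatment arm stays at 0.60. Power at 165 per group uses the corrected size m = 165·[1 − 1/(165·d)]² in the formula above, solved for power.

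| c (assumed) | Control prevalence | Difference (points) | Power, one-sided, corrected | Power, two-sided, corrected |
|---|---|---|---|---|
| 0 | 75.0% | 15.0 | 88% | 80% |
| 5% | 74.25% | 14.3 | 84% | 75% |
| 10% | 73.5% | 13.5 | 80% | 70% |
| 20% | 72.0% | 12.0 | 71% | 59% |

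At 20% uptake the loss is 17 points one-sided and 21 points two-sided. If buyers gained only half the effect, 20% uptake would lower control prevalence by 0.15 × 0.20 × 0.5 = 1.5 points, which is the 10% row.

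**The case against.** The strongest reply is that the texts can be reconciled. Section 8 may describe only what the lottery allocates, so that not receiving means not receiving free. The free ration covers children aged 2 to 5, so the purchase in section 10.4 could be additional product for the household. Treatment would then get a free ration and could buy more, and controls would get nothing free and could buy. The overall objective is a value-chain contract and the main outcome is meeting the milk target, so purchase at own cost could be a deliberate part of the control condition. Much of this stands, and a reader who infers that the sections cannot all be followed goes too far. But the protocol never states this reading, and adopting it would make the Summary's description of the control arm inaccurate and leave section 7 without an allowance.

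Two other inferences also go too far.
- That treatment households keep buying in withheld weeks, which would undercut the milk incentive. Section 10.4 is silent on this.
- That power starts at 80% under the plan as written. That holds only for the two-sided test. Under the stated one-sided test it starts at 88% and is still 80% at 10% uptake.

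It is also fair to say that the table is an upper bound for each uptake rate. Section 7 doubts that even free product will be eaten every day, and a household that pays may use less. Finally, the planned questionnaires cover food consumption and dietary diversity, and a Thiakry item may exist in the instrument, which is not shown. The absence of such an item from the protocol is therefore no separate fault.

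**Conclusion.** The point holds as an unresolved inconsistency in the rule that defines the contrast. Section 10.1 opens purchase to controls, against the plain sense of the Summary and section 8. Section 10.4 has the treatment group buying what sections 8 and 10.1 call free. If controls may buy, the anemia difference is diluted toward zero and section 7 has not allowed for it.

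The size is unknown because no uptake figure is given. Under the full-effect assumption, uptake of 5 to 20% costs 0.75 to 3 points of the 15-point difference, with the power losses tabulated above. Those figures rest on section 7's prevalences and 165 per group before clustering. For the milk outcome, the documents show only that the incentive is ambiguously described; they do not show that it is weakened. The matter should be corrected, but it does not by itself invalidate the trial.

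**What to change.** 1. Reconcile the Summary and sections 8, 10.1 and 10.4 into one access rule covering both arms. It should state whether treatment households may buy and whether that applies in weeks when the bonus is withheld. Use the same wording at every route meeting.
2. Then choose one of two routes.
   - To keep the contrast that the Summary, section 7 and section 8 describe, remove the study's offer of sale to control households at the meeting and from the truck. This should cover at least the January to July 2013 distribution phase. If section 8 means the whole study literally, it should run to the January 2014 round. Section 8 already provides compensation for controls at the end.
   - If control purchase is intended, restate the comparator as no free product with purchase allowed, and restate the section 7 assumption with an explicit uptake range.
3. Under either route, include one question on Thiakry bought or eaten by the children in the July 2013 and January 2014 questionnaires, in both arms. Analyse all households as randomised, and use the answers to describe exposure, not to reassign or exclude.

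The cost is wording in four places and one questionnaire item, plus forgone sales to control suppliers under the first route. The second route may require a larger sample.

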**10.2.** **Awareness-raising campaign**

An awareness campaign will be implemented in the area by the Cellule de Lutte contre la Malnutrition (Unit for the Fight against Malnutrition; CLM) in December 2012, through community representatives of the Association Sénégalaise pour le Bien-Etre Familial (Senegalese Association for Family Well-Being; ASBEF), to inform mothers on good feeding practices and explain issues related to anemia. The awareness campaign will be conducted throughout the duration of the study through discussion groups at markets, health centers, and gathering areas, and through radio advertisements.

**10.3.** **Malaria, schistosomiasis, helminths**

As anemia often has multifactorial causes, the WHO recommends an integrated approach to fight against anemia (WHO/UNICEF, 2004). To assess the impact of distributing fortified Thiakry on anemia in the study area, it is necessary to take into account the risk of infection through malaria and helminth infections such as schistosomiasis, which may vary from one zone to the other (Staubli, 2001).

Malaria in Senegal is seasonal, with a higher transmission in the south than in the north and higher levels during the rainy season than during the dry season. In northern Senegal, despite a fairly desert-like environment, the presence of flooding rivers during the rainy season, as well as irrigation practices and seasonal migration, contribute to the transmission of the parasite. However, the transmission remains very low in the area of Richard Toll, averaging 1.2 cases per 1000 inhabitants (Diop, 2012). According to the 2008-2009 DHS data, the national prevalence of malaria at the time of the survey was 5.7%. The lowest levels were found in the region of Saint-Louis (the region where Richard Toll is located), where no cases were detected, and in the regions of Dakar (0.8%) and Louga (1.4%) (DHS, 2008). This success can be attributed to the strong involvement of local institutions, who provide excellent distribution of impregnated mosquito nets during prenatal consultations for women and enable access to effective antimalarials and rapid diagnostic tests, without supply disruptions (Diop, 2012). In our study, which will take place exclusively during the dry season, we can therefore reasonably not take into account the effect of malaria on anemia.

On the other hand, irrigation practices have drastically increased cases of schistosomiasis in the area of Richard Toll. However, as cases of schistosomiasis are most frequent among young boys who become infected while working in the fields, it is unlikely that our study population (children ages 2 to 5 years) is confronted with this parasitic disease. We can also ignore the effect of bilhiarzose in our study of anemia. Finally, for other common helminth infections in children (roundworm, hookworm, Trichinella), deworming with mebendazole is advocated for children over one year of age (WHO, 2003). The establishment of a mebendazole distribution during the first round of household data collection for children included in the study (if they did not receive treatment during the last 3 months) will allow for comparability of children concerning this factor, at the beginning of the study.

**10.3. First household data collection (Baseline)**

An initial survey of households will take place in January 2013 to gather baseline data. The questionnaire, in Fulani, will collect data related to:
- Composition of the household
- Herding/cows (size of herd, etc.)
- Crops (crop type, etc.)
- Socioeconomic status (household goods, level of education, etc.)
- Household food consumption (frequency, food security, etc.)

Additionally, measurements of hemoglobin levels will be conducted for children 6 months to 5 years, as well as their mothers, by drawing a drop of blood using a lancet and placing it in a microcuvette, allowing a direct reading of the result using a HemoCue® Analyzer

**10.4.** **Intervention**

The distribution phase of the incentive will last 6 months, from January 2013 to July 2013. The incentive of fortified Thiakry will be distributed daily by the milk collectors. Participants in the study who are part of the treatment group will have the daily opportunity to buy fortified Thiakry directly from the milk collection truck. During the study, if a herder responsible for the milk container has committed to providing a certain quantity of milk daily to LDB and does not honor their commitment one or two days in the same week, they will receive a warning (if they are in the treatment group). If the herder does not provide milk for 3 or more days in the week and is in the treatment group, they will not receive the fortified Thiakry the following week.

**10.5. Second household data collection**

A second phase of data collection will take place amongst households in July 2013, with a questionnaire and hemoglobin measures.

**10.6. Third household data collection**

A third phase of data collection will take place amongst households in January 2014, with a questionnaire and hemoglobin measures.

# 11. Biometrics and data analysis

**11.1. Results analysis plan**

A descriptive analysis will first be carried out, along with a comparison of baseline characteristics between both groups: proportion of children who are anemic, average hemoglobin levels, attrition of households etc. Covariates collected during the study at baseline (socio-economic level of the household, household composition etc.) corresponding to the two groups will be compared through univariate analysis. The efficacy of treatment will be evaluated using an adjusted multivariate analysis, adjusting using covariates that may have a confounding factor: length of participation in the study or covariates whose distribution is different between the 2 groups.

The analyses will be performed on the main response variable "proportions of households respecting the contract outlined at the beginning of the study", in terms of volume and milk collection frequency. These proportions will be compared between the two groups.

Secondary responses variables (proportion of children presenting mild, moderate or severe anemia; proportions of children with stunting, undernutrition or wasting) will be analyzed on the intent-to-treat population, gathering all the children who were attributed to a group for whom hemoglobin measurement results are available over 6 months, regardless of the group. The analysis will be adjusted for age and risk factors for anemia if their distributions are different between the two groups.

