In 2006, the Laiterie du Berger (LDB), a social venture later supported by Danone Communities, Credit Agricole, the Grameen Foundation, and other partners, started to collect milk from pastoralist households living near the town of Richard Toll in the Senegal River Valley. LDB’s business model is to produce high-quality products (primarily yogurt) for mostly urban populations, using fresh milk that it collects itself twice a day from households living within 50 km of its processing plant. Over the years, LDB has built up a reliable base of 700 milk suppliers on 4 main collection routes. At the end of the month, suppliers come to LDB and collect the payment for their month’s production. Part of these payments can be used to purchase discounted animal feeds, which appears to be an important incentive for suppliers. They may also receive an in-kind advance (in animal feeds) of up to 30% of the past month’s production, if they face specific liquidity and/or animal feed needs.

The current study aims to test a type of incentive among farmers to encourage them to provide milk to LDB more regularly during the dry season, while investigating and explaining the mechanisms involved. The incentive will be distributed as a bonus, after a contract with a target volume (corresponding to 1 liter of milk per lactating cow per day) and regularity in the frequency of milk collection has been agreed upon at the beginning of the dry season. The incentive tested will be a dairy product produced by LDB itself: fortified Thiakry. This form of incentive corresponds to the "Value Chain" concept^^[[1]](#footnote-1)^^: the initial product is the milk produced by herders and the processing of the milk produces in yogurt to which millet and fortification are added. This results in a final value-added product (fortified Thiakry) that will be made accessible to herders.

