**11.2. Methods and data analysis models**

The impact of the intervention will be analyzed using the "difference in differences" method: the difference in the prevalence of anemia for children 2 to 5 years or the difference of average hemoglobin levels, i) between the treatment and the control group and ii) between the beginning and the end of the intervention. It will be possible to use a propensity score, determined from the baseline characteristics, in order to check the comparability between groups and, if necessary, to use the score as an adjustment factor. All tests performed will be unilateral, with a 95% confidence interval. The analysis will be performed using STATA 12.0 (Stata statistical software, Stata Corporation, College Station, Texas USA).

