**11.3. Attrition**

Attrition will comprise households who have moved out of the area reached by collection routes and/or who have decided to go on transhumance and to leave the study voluntarily. The reasons for attrition will be recorded by enumerators. The characteristics of these households will be compared with those of households who participated all the way to the end of the study.

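### Length of participation, a post-lottery variable tied to the main outcome, is listed as a confounder in the efficacy model; adjusting for it can bias the treatment effect

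*Protocol*

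**What the plan says.** Section 11.1 states the efficacy model in one general sentence: "The efficacy of treatment will be evaluated using an adjusted multivariate analysis, adjusting using covariates that may have a confounding factor". The covariates it then names are "length of participation in the study or covariates whose distribution is different between the 2 groups". Length of participation is not defined further.

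The same section says that the baseline covariates "corresponding to the two groups will be compared through univariate analysis". For the child outcomes it adds: "The analysis will be adjusted for age and risk factors for anemia if their distributions are different between the two groups". Section 11.2 allows a propensity score built from baseline characteristics and, "if necessary, to use the score as an adjustment factor". No threshold for a difference is given, and the list of baseline covariates is left open.

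On timing, section 8 says: "The two groups will be chosen by lottery at the first information-sharing meeting". Under section 11.3, participation ends when a household moves beyond the collection routes, or for those "who have decided to go on transhumance and to leave the study voluntarily". The main outcome (section 3) is the proportion of herders who reach their contract objective for volume and frequency across the study period. Section 1 gives the purpose of the incentive: "to encourage them to provide milk to LDB more regularly during the dry season".

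**The concern.** A confounder must be able to influence, or share a cause with, the allocation. How long a household stays is determined after the lottery, so it cannot do this. It can only be a consequence of allocation, a marker of household engagement, or both.

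That matters because a household that leaves stops delivering, so length of stay is close to a component of contract success. If the incentive keeps some households in the study, comparing arms at equal length of stay discards that benefit. It also compares unlike households. Those held in by the incentive sit beside control households that stayed without it, and the latter are on average more engaged or more sedentary. Both mechanisms pull the estimate down when the incentive lengthens participation.

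An effect on participation is plausible under this design. Households learn their arm at the first meeting, before they return the signed form. Warnings and withheld product apply only to the treatment group (section 10.4). Leaving is not expected to be rare: section 7 plans for 20% attrition.

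The rule of adjusting for baseline covariates only when they differ raises a separate and smaller issue, namely a model chosen after seeing the data.

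**Working it through.** The protocol gives no figure for this point, so there is nothing of its own to reproduce. The calculations below use assumed values to show direction and rough size.

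**1. Contract outcome, adjusting for participation**

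Assumptions: unmeasured engagement U is standard normal. A household participates fully (F = 1) when U plus independent standard normal noise exceeds a cut-off. Full participation is 70% in control and 70%, 80% or 90% in treatment. The probability of contract success is 0.40 + 0.10·T + 0.15·F + 0.10·U, where T = 1 for treatment.

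*Unadjusted (total) effect* = 0.10 + 0.15 × (difference in full participation). For 90% against 70% this is 0.10 + 0.15 × 0.20 = 0.130.

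*Adjusted effect, 90% against 70%.* The mean of U given F = 1 is 0.7071·φ(z)/P(F = 1), and given F = 0 it is −0.7071·φ(z)/P(F = 0).
- Control: φ(z) = 0.3477, giving 0.351 (F = 1) and −0.820 (F = 0).
- Treatment: φ(z) = 0.1755, giving 0.138 (F = 1) and −1.241 (F = 0).
- Difference within F = 1: 0.10 + 0.10 × (0.138 − 0.351) = 0.0787.
- Difference within F = 0: 0.10 + 0.10 × (−1.241 + 0.820) = 0.0579.
- Least-squares weights: 0.9 × 0.7/1.6 = 0.394 and 0.1 × 0.3/0.4 = 0.075.
- Weighted result: (0.394 × 0.0787 + 0.075 × 0.0579)/0.469 = 0.075.

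Of the fall from 0.130 to 0.075, 0.030 is the removed effect through staying (0.130 to 0.100) and 0.025 is selection on engagement (0.100 to 0.075).

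A simulation of 2,000,000 households per scenario agrees within its sampling error (standard error about 0.0007):

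| Full participation, control / treatment | Unadjusted | Adjusted for participation |
|---|---|---|
| 70% / 70% | 0.100 | 0.100 |
| 70% / 80% | 0.116 | 0.089 |
| 70% / 90% | 0.131 | 0.077 |

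**2. Continuous outcome**

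Assumptions: a direct effect of 0.20, an arm effect on length of 0.5, effects of U of 0.5 on length and 0.3 on the outcome, and a residual variance of 1 for length. The adjusted coefficient is 0.20 − 0.5 × [0.3 × 0.5/(0.25 + 1)] = 0.20 − 0.06 = 0.14. Simulated total effects of 0.20, 0.25 and 0.30 all gave about 0.14 after adjustment. With no arm effect on length, a true 0.20 stayed at 0.20.

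**3. Adjusting for a baseline covariate only when imbalanced**

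Assumptions: 20,000 trials of 430 independent children (the count in section 7, ignoring clustering), with the covariate entered only if its imbalance has |z| > 1.96.
- Mean estimate for a true 0.20: 0.199 to 0.200, so no bias.
- Type I error for covariate-outcome correlations of 0, 0.3, 0.5 and 0.7: two-sided 0.050, 0.051, 0.041 and 0.036; one-sided (the protocol plans unilateral tests) 0.050, 0.050, 0.045 and 0.042.
- Precision at correlation 0.7: the standard deviation of the estimate is 0.00063 × √20,000 = 0.089 under the imbalance rule, against √[(1 − 0.49) × 4/430] = 0.069 if the covariate is always adjusted for. At correlation 0.5 the figures are 0.094 and 0.084.

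**The case against.** The strongest reply is that the protocol never says the incentive is meant to prolong participation. It targets volume and regularity of delivery. Missed deliveries cost a treated herder a warning or a week of product, not a place in the study, and exit is by moving, transhumance or choice. This stands: an effect of arm on length is an inference, and without one there is no bias. It does not make length a valid confounder.

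It is also unclear which model uses length. For the milk outcome section 11.1 says only that the proportions will be compared. For the child outcomes it gives a separate set without length, and restricts the population to children with hemoglobin results over 6 months, which probably narrows the variation in length. This too stands in part. The general efficacy sentence nevertheless governs at least one of the outcomes, and nothing limits it to baseline covariates.

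Three stronger readings are tempting and are not supported:
- **The effect would change sign.** Simulations in which the incentive acts only through retention can turn a true gain of 4 to 10 percentage points into an estimate of −1 to −5. That depends on the assumed strength of the motivation and retention paths, for which the protocol has no figures. The calculations above show attenuation without reversal.
- **Imbalance-triggered adjustment biases the effect.** Step 3 shows that it does not. Because allocation is known before the forms come back, enrolment could differ by arm, so checking balance is itself reasonable.
- **Baseline hemoglobin is ignored when balanced.** The difference-in-differences analysis in section 11.2 brings baseline anemia or hemoglobin in whatever the balance.

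Finally, a detailed covariate list is often left to a statistical analysis plan. Here, however, section 11.1 itself states the selection rule and names length.

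**Conclusion.** Naming length of participation as a confounder is wrong as written and should be corrected. Adjusting for it can bias the treatment effect and means that the model no longer estimates the intention-to-treat effect. This holds if the arm affects how long households stay, which the design makes plausible but the protocol does not state. If the incentive lengthens participation and engagement raises both staying and success, the effect is attenuated. Under the assumed values, the loss is about a quarter with a 10-point difference in full participation (0.116 to 0.089) and about two fifths with a 20-point difference (0.131 to 0.077). The true size cannot be derived from the protocol. The concern is strongest for the milk outcome, where staying is nearly part of success, and weaker for anemia.

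The imbalance rule is a lesser matter. It leaves the model dependent on the data and the analyst's discretion, loses precision, and makes the test somewhat conservative when covariates are strongly prognostic.

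**What to change.** 1. In section 11.1, delete length of participation from the adjustment set. Report it by arm as an outcome or with the attrition results. Section 11.1 already lists household attrition among its between-group comparisons, and section 11.3 already records reasons for leaving.
2. State that the efficacy model uses baseline covariates only, and say which outcomes it covers.
3. Replace the imbalance rule in section 11.1, and the conditional use of the propensity score in section 11.2, with a fixed set applied whatever the balance. Examples are age and collection route for the children, with baseline anemia or hemoglobin handled by the planned difference in differences or as a covariate, and herd size and collection route for milk. Balance can still be described.

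The cost is a few sentences in sections 11.1 and 11.2. Herd size, household composition and hemoglobin are in the baseline survey, and the routes are known, so no new data are needed. Household-level delivery history is better not relied on, because section 5 has about two households sharing a container.
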